**Fig. 2 FI210067-2:**
[figure not shown]
Time points (T) of laboratory tests during individual PK-profiling. A preinfusion,
*t*
 = 15–30 minutes and t = 4 hours sample (left) are performed in all patients. The other time points (right) depend on hemophilia type and brand of factor concentrate. EHL, extended half-life; PK, pharmacokinetic; SHL, standard half-life.

Dosing will be advised by clinical pharmacologist on the basis of FVIII/FIX target trough levels as set by treating physician, in accordance to patient characteristics, previous trough levels (if a patient switches between factor concentrates), bleeding history, activity pattern, and in consultation with patient/caretakers. If desirable, physicians are also able to set FVIII/FIX target peak levels during intensive physical activities. In this way, treatment is truly customized and tailored to the needs and lifestyle of each individual as personalization is meant to be. Retrospective data of a patient, such as previous trough levels and factor levels at onset of a bleed or during sport activities, can be informative to the physician to set target levels.

Thereafter, patients will initially be on PK-guided treatment for 12 weeks. During these 12 weeks, a minimum of three factor levels will be measured and compared with predicted FVIII/FIX values to validate predicted dosing regimen (
Table 3
). Patients on EHL will be on iterative PK-guided treatment with dose adjustment if needed based on both factor levels and bleedings. Iterative treatment is desirable in these patients as most patients initiate treatment with EHL factor concentrates after being on prophylaxis with SHL factor concentrates. Because of the lack of knowledge of most optimal (frequency and dose of) EHL factor concentrate, this period has a dose finding perspective.

For patients on SHL predicted FVIII/FIX values will be blinded to the treating physician and dosages will not be adjusted during the first 10 weeks. Thereafter, dose adjustment can be made.

A subsequent follow-up period of 24 weeks on PK-guided treatment is necessary to further collect data to establish the associations between FVIII/FIX levels and bleeding events. Only if clinically indicated, FVIII/FIX levels will be measured during bleeds (
Table 3
). At the end of this follow-up period, one final blood sample will be taken to compare the factor level with the predicted value (
Table 3
). Patients/caretakers will again fill in the HAL or PedHAL questionnaire and the physiotherapist will perform the HJHS to evaluate outcomes after implementation of PK-guidance.

Finally, at the end of the study, both patients/caretakers and the treating physician will fill in the VAS questionnaire, considering the experience with PK-guided dosing and EHL factor concentrate when patients have switched to an EHL factor concentrate.

Importantly, hemophilia patients, who have undergone individual PK-profiling prior to study inclusion or who have already received PK-guided treatment on SHL or EHL concentrate, are also able to participate in the study. PK profiling is required to be performed with a maximum of 1 year prior to study inclusion when <12 years of age and a maximum of 3 years prior to study inclusion when 12 years and older. Patients who already received PK guidance prior to study inclusion, will only complete the VAS questionnaire at the end of the study period, since asking the patient questions with regard to expectations on PK-guided dosing at the beginning of the study would lead to recall bias. Also, the HJHS will not be performed in these patients and PedHAL will not be completed in this subgroup as results after body weight (and bleeding) –based prophylaxis and PK-guided therapy cannot be compared.

In parallel with the prospective study, retrospective data analysis will be performed over a 12-month period prior to inclusion (if no PK profiling has been performed) or from PK profiling prior to inclusion. These data will be utilized as “real-world data” to construct and enrich available population PK models. Moreover, if patients kept a detailed patient log-on infusion dates and timing and bleeding episodes, annualized (joint) bleeding rate (A(J)BR) FVIII/FIX trough levels and FVIII/FIX levels during physical activities and at the onset of a bleed can be calculated.

Factor activity levels will be measured by local laboratories, as this reflects the real-world setting of standard clinical practice. Plasma samples are stored in case centralized measurements are deemed necessary. Laboratory specifications (assay, reagents, deficient plasma, and analyzer) applied in local laboratory will be recorded precisely. Preferably, the local laboratory assays match with the assays as used during population PK model construction.

### Bayesian Forecasting

Bayesian forecasting will be performed with the NONMEM software (Icon, Dublin, Ireland); individual PK parameters will be assessed with a limited number of blood samples. Available population PK models in literature and new models that will become available will be used. Based on the estimated individual PK parameters and the FVIII/FIX target trough and peak values as set by the physician, dosing schedules will be calculated.

#### Sample Size Calculation

In this prospective study, we aim to evaluate the predictive performance of PK-guided dosing in hemophilia patients. It is not common practice to calculate a sample size for prognostic models, and, to the best of our knowledge, it is not possible to calculate a sample size for the determination of predictive performance. What we do know is that as characteristics, such as age, body weight, activity pattern, and bleeding phenotype, are not part of the inclusion or exclusion criteria, the study population will be a reflection of the real-world and thus a heterogeneous hemophilia population. However, we aim to enroll a minimum of 50 patients in all strata together to explore the predictive performance of PK-guided dosing in real life.

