## Abstract

In resource-rich countries, almost all severe hemophilia patients receive prophylactic replacement therapy with factor concentrates to prevent spontaneous bleeding in joints and muscles to decrease the development of arthropathy and risk of long-term disability. Pharmacokinetic (PK)-guided dosing can be applied to individualize factor replacement therapy, as interindividual differences in PK parameters influence factor VIII (FVIII) and FIX activity levels. PK-guided dosing may therefore lead to more optimal safeguarding of FVIII/FIX levels during prophylaxis and on demand treatment. The OPTI-CLOT TARGET study is a multicenter, nonrandomized, prospective cohort study that aims to investigate the reliability and feasibility of PK-guided prophylactic dosing of factor concentrates in hemophilia-A and -B patients in daily clinical practice. At least 50 patients of all ages on prophylactic treatment using standard half-life (SHL) and extended half-life (EHL) factor concentrates will be included during 9 months and will receive PK-guided treatment. As primary endpoint, a minimum of four FVIII/FIX levels will be compared with FVIII/FIX levels as predicted by Bayesian forecasting. Secondary endpoints are the association of FVIII and FIX levels with bleeding episodes and physical activity, expectations and experiences, economic analyses, and optimization of population PK models. This study will lead to more insight in the reliability and feasibility of PK-guided dosing in hemophilia patients. Moreover, it will contribute to personalization of treatment by greater knowledge of dosing regimens needed to prevent and treat bleeding in the individual patient and provide evidence to more clearly associate factor activity levels with bleeding risk.

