### Outcome Measures

#### Primary Endpoints

Observed FVIII and FIX levels in comparison to FVIII and FIX levels are predicted by Bayesian forecasting. The predictive performance is deemed acceptable when at least 80% of the actual FVIII/FIX levels are within ± 25% of the predicted (target) values as stated by treating professional.

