**Fig. 1 FI210067-1:**
[figure not shown]
Flow chart. EHL, extended half-life; HAL, Hemophilia Activity List; HJHS, Hemophilia Joint Score; PedHAL, pediatric HAL; PK, pharmacokinetic(s); SHL, standard half-life; VAS, visual analogue scale *Non severe hemophilia patients will be analyzed separately. **In parallel with the prospective study, retrospective data analysis will be performed over a 12 month period prior to inclusion (if no PK profiling has been performed) or from PK profiling prior to inclusion. ***Patients in stratum 2 could undergo PK profiling during SHL prophylaxis as well as during EHL prophylaxis.

Patients/caretakers will fill in the Hemophilia Activities List (HAL) and/or pediatric HAL (PedHAL) before initiation. Moreover, the Hemophilia Joint Health Score (HJHS) will be performed or must have been performed <12 months prior inclusion.

The validated PedHAL/HAL questionnaire and the HJHS are included as clinical parameters to systematically establish baseline values of functional outcome from the patient's perspective and to be informed of joint status, respectively. These clinical parameters may help to evaluate outcomes after implementation of PK guidance.

Furthermore, both patients/caretakers and the treating physician will fill in a specifically developed questionnaire using VAS scales, before the implementation of PK-guided dosing, considering the expectations with PK-guided dosing of prophylaxis. More specifically, in the questionnaire, questions are asked about satisfaction, being informed of factor levels, and expected burden of PK guidance. Moreover, when patients switch to an EHL factor concentrate, the reasons for switching are also asked.

An individual PK profile will be constructed after a factor concentrate dose of 35 to 50 IU/kg, depending on hemophilia type and age of the patient. The frequency and timing of blood sampling during PK profiling is depending on type of hemophilia and type of factor concentrate (
Fig. 2
). No wash out period is required if three prior infusions and time points of infusion are documented. During sampling of the PK profile, laboratory tests will be performed according to
Tables 1
and
2
.

**Table 1 TB210067-1:** Laboratory tests during individual PK profiling for patients with hemophilia A

On FVIII-SHL	Preinfusion	T = 15–30 minute	T = 4 hours	T = 24 hours	T = 48–72 hours	
On FVIII-EHL	Preinfusion	T = 15–30 minute	T = 4 hours	T = 24 hours	T = 48 hours	T = 72–96 hours a
ASAT	X					
ALAT	X					

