a Only in case of an EHL concentrate.

**Table 3 TB210067-3:** Laboratory tests during initial PK-guided treatment and follow-up

	Initial PK-guided treatment (12 weeks)			Follow-up treatment under PK guidance (24 weeks)	Bleeds (only when blood sampling is clinically indicated, during total study period)
Visit	1	2	3	1	additional
Hemophilia A					
FVIII	X	X	X	X	X
FIX					X
VWF:Ag					X
VWF:Act					X
VWF:CB					X
VWFpp					X
APTT	X	X	X	X	X
Inhibitor FVIII	X			X	(X)
Max of 10-mL citrate plasma	X	X	X	X	X
Hemophilia B					
FIX	X	X	X	X	X
FVIII					X
VWF:Ag					X
VWF:Act					X
VWF:CB					X
VWFpp					X
APTT	X	X	X	X	X
Inhibitor FIX			X	X	(X)
Max of 10-mL citrate plasma	X	X	X	X	X

Abbreviations: APTT, activated partial thromboplastin time; FIX, factor IX; FVIII, factor VIII; PK, pharmacokinetic; VWF:Act, von Willebrand factor activity; VWF:Ag, von Willebrand factor antigen; VWF:CB, von Willebrand factor collagen binding; VWFpp, von Willebrand factor propeptide.

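### The primary endpoint is a proportion judged against 80%, so its precision can be calculated; the protocol says no sample size can be, and gives its verdict on a point estimate of clustered levels with no interval

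*Protocol article*

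**What the plan says.** All references are to the protocol article.

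- **Sample Size Calculation:** a statement, hedged as being to the authors' knowledge, that "it is not possible to calculate a sample size for the determination of predictive performance". The number that follows is "we aim to enroll a minimum of 50 patients in all strata together", described as serving to explore predictive performance. No power, alpha, precision target or minimum per stratum accompanies it.
- **Primary Endpoints, repeated in Statistical Analysis:** "The predictive performance is deemed acceptable when at least 80% of the actual FVIII/FIX levels" fall within ±25% of the predicted (target) values. The unit counted is the level.
- **Number of levels:** the Abstract says "a minimum of four FVIII/FIX levels will be compared with FVIII/FIX levels as predicted by Bayesian forecasting". Interventions breaks this down: in the first 12 weeks "a minimum of three factor levels will be measured and compared with predicted FVIII/FIX values", and one more sample at the end of follow-up is compared with its prediction.
- **Intervals:** Statistical Analysis names one 95% CI, for the mean error (bias). None is attached to the percentage within ±25%.
- **Subdivision:** Interventions stratifies by hemophilia type and by SHL or EHL concentrate. Statistical Analysis will investigate and describe differences between concentrates and age groups. The Fig. 1 footnote adds "Non severe hemophilia patients will be analyzed separately".

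**The concern.** The reason given for having no calculation does not fit the endpoint. A share of levels compared with a fixed 80% bar is a single proportion, and its precision and the behaviour of the decision rule are standard calculations. The protocol supplies the number of patients and of levels per patient. Only the ICC has to be assumed, and a range deals with that.

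The rule is also stated on the observed percentage alone. Each patient contributes at least four levels, all predicted from that patient's own estimated PK parameters, so hits and misses are likely to cluster. The effective sample size is then below 200. A report could call performance acceptable without showing how far below 80% the truth might lie. The planned comparisons by concentrate and age group rest on still fewer patients.

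**Working it through.** **No figure to reproduce.** The 50 is given without inputs, so the check is of what 50 delivers.

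**Inputs from the protocol**
- 50 patients (minimum): Sample Size Calculation.
- 4 levels per patient (3 + 1, minimum): Abstract and Interventions. Total 50 × 4 = 200 levels.
- Bar of 80%: Primary Endpoints.

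**Assumptions, not in the protocol**
- ICC of within/outside ±25% inside a patient: 0, 0.2 and 0.4.
- Four equal strata (2 hemophilia types × 2 concentrate types), so 12.5 patients and 50 levels each. The flow chart is not shown and no stratum sizes are given.
- No dropout.

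**Step 1. Precision at an observed 80%**

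Design effect DE = 1 + (4 − 1) × ICC. Effective n = 200/DE. Half-width = 1.96 × √(0.80 × 0.20 × DE / n), with n = 200 overall and n = 50 per stratum.

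| ICC | DE | Effective n (overall) | Half-width, 200 levels | Half-width, 50 levels |
|---|---|---|---|---|
| 0 | 1.0 | 200 | ±5.5 points | ±11.1 points |
| 0.2 | 1.6 | 125 | ±7.0 points | ±14.0 points |
| 0.4 | 2.2 | 91 | ±8.2 points | ±16.4 points |

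Example: 1.96 × √(0.16 × 1.6 / 200) = 1.96 × 0.0358 = 0.070. As a check on the normal approximation, the Clopper-Pearson interval for 160/200 is 73.8% to 85.3%.

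**Step 2. How often the point-estimate rule passes**

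The rule passes when at least 160 of 200 levels are within ±25%. ICC 0 uses the exact binomial tail. ICC 0.2 and 0.4 use a beta-binomial with four levels per patient, summed over 50 patients.

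| True share | ICC 0 | ICC 0.2 | ICC 0.4 |
|---|---|---|---|
| 70% | 0.1% | 0.7% | 1.8% |
| 75% | 5.8% | 10.8% | 14.8% |
| 78% | 27.9% | 32.6% | 35.3% |
| 80% | 54% | 54% | 54% |
| 85% | 98% | 94% | 91% |

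**Step 3. What an interval-based reading would require**

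For the lower 95% bound to reach 80%, the observed share must be about 86% (172/200) with independent levels. Applying the exact interval to the effective n, it is about 88% at ICC 0.3.

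**Step 4. A sample size can be written down**

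Patients for a half-width h with four levels each = (1.96² × 0.16 / h²) × DE / 4. For h = 0.05, 1.96² × 0.16 / 0.0025 = 245.9 levels. That gives 245.9 × 1.0 / 4 → 62 patients at ICC 0, 245.9 × 1.6 / 4 → 99 at ICC 0.2, and 245.9 × 2.2 / 4 → 136 at ICC 0.4. This shows only that the calculation exists; the protocol sets no ±5 target.

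**The case against.** **The sentence is hedged and the aim exploratory.** This stands. With no stated calculation there is no arithmetic error, and 50 is a defensible exploratory minimum. But the hedge does not make the statement right for the endpoint the protocol defines, and the Introduction goes beyond exploration in aiming to prove reliable prediction.

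**Intervals and clustering could be in an analysis plan that is not shown.** This also stands: their absence alone would not be a finding. The point rests on what the article itself states and fixes, namely the impossibility claim and a binary verdict on the observed percentage, beside an interval specified only for the mean error.

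**The rule rarely passes poor performance.** Fair: a true 70% passes in under 2% of studies over ICC 0 to 0.4, and pooled precision is moderate. The weak discrimination lies close to the bar and in the subgroups.

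**The stratum figures are hypothetical.** They depend on four equal strata. The 80% rule is not said to apply per stratum, and the comparisons are to be described, not tested. Even so, a stratum of 50 independent levels has a half-width of ±11 points.

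**A stronger reading that fails.** A reader might infer that extra levels distort the endpoint because they are drawn when something has gone wrong. The protocol does not support this. Bleed samples are described in connection with follow-up for bleeding associations. PK profiling on two concentrates is planned for one stratum and provides the basis for individual dosing. Iterative EHL dosing is not said to add levels. Interventions ties comparison with prediction to the 12-week levels and the final sample. The word minimum leaves the exact set of counted levels open, and no more than that.

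**Conclusion.** The concern holds in limited form. For this endpoint, precision and sample size can be calculated, so the reason given for having no calculation is wrong. The acceptability verdict is fixed on a bare percentage of levels clustered within patients. Overall precision is moderate and subgroup precision is poor if strata are anything like equal quarters of the cohort. An observed 80% would be reported as acceptable although, even with independent levels, the data would be compatible with a true value of about 74%.

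The pooled figures rest on the two planned minimums (50 patients, four levels) and an assumed ICC of 0 to 0.4; more patients or levels would improve them. The documents do not show that 50 is too few for exploration, or that bleed or profiling samples enter the primary analysis.

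**What to change.** - **Sample Size Calculation:** replace the impossibility sentence with a precision statement. For example: with at least 50 patients and four levels each, an observed 80% has a 95% half-width of about ±5.5 points at ICC 0, ±7.0 at 0.2 and ±8.2 at 0.4. Declare the ICC range as an assumption, and keep 50 as an exploratory minimum.
- **Primary Endpoints and Statistical Analysis:** report the percentage within ±25% with a patient-clustered 95% CI (GEE or a bootstrap over patients), and use the same clustering for the CI of the mean error. State that a pass on the point estimate is exploratory unless the lower bound also reaches 80%.
- **Comparisons by concentrate and age group:** label them descriptive and show their intervals.
- **Levels counted:** say that the primary analysis uses the levels scheduled for comparison with prediction (at least three in the 12 weeks plus the final sample) and not bleed-triggered samples. This is a clarification, not the repair of a demonstrated error.

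Enrolment and sampling are unchanged. The cost is a little analysis work and a stated precision that looks less favourable than a bare percentage.

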### Statistical Analysis

Continuous data will be expressed as mean and standard deviation when normally distributed or median and interquartile range when not normally distributed. Categorical data will be expressed as frequency and percentage.

As described in the primary study endpoint, the predictive performance of PK-guided dosing is deemed acceptable when at least 80% of the actual FVIII/FIX levels are within ± 25% of the predicted (target) values as stated by treating professional. Both the mean error between the predicted and observed factor level and the mean absolute difference of the predicted level will be calculated. No significant bias presented as zero is included in the 95% confidence interval (CI) of the mean error. Moreover, differences between the predictive performance of different factor concentrates and age groups will be investigated and described.

Association of factor levels with bleedings will be described according to sub classifications. Comparisons of the ABR and joint status before and during PK-guidance will be analyzed using a paired
*t*
-test or Wilcoxon's test, depending on the distribution.

R (version 4.0.3) will be used for statistical analysis.

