PK-guided dosing may help achieve higher trough levels more efficiently when clinically indicated, as well as provide guidance when patients switch to alternative replacement factor concentrates, while taking cost and benefit of treatment into account. In addition, PK-guided dosing may lead to increased insight into the association between FVIII/FIX levels, bleeding (risk), and physical activity levels in individual patients as factor levels can be predicted at any time point and related to bleeding and activity. Therefore, we aim to prove that FVIII/FIX trough and peak levels as set by treating physician can be predicted and achieved reliably by application of PK-guided prophylaxis and that this intervention is feasible for patients and treatment teams.

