#### Secondary Endpoints

The four secondary endpoints are briefed below:

Association of (real world or predicted) FVIII/FIX levels with bleeding episodes and daily activities. Additionally, bleeds will be categorized according to the following subclassifications: total number of bleeds over time, number of spontaneous bleeds, number of traumatic bleeds, number of joint bleeds, number of target joint bleeds, and bleed severity.Expectations, feasibility, and experience with PK-guided dosing with the different factor concentrates (SHL vs. EHL) as reported by patient/caretakers and physician will be measured using a visual analogue scale (VAS) questionnaire at the start and end of the study.Economic analysis in which costs and benefits of standard prophylactic treatment and PK-guided prophylaxis are compared.Analysis of described modifiers effecting PK parameters of FVIII/FIX concentrate to further optimize population PK models. Modifiers include demographics (such as lean body mass) and laboratory measurements (such as the von Willebrand Factor levels).

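### Describing bleeds by type, with rates per calendar time only, cannot separate risk at a factor level from time spent at that level, so it does not support the bleeding-risk claim

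*Protocol article*

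**What the plan says.** The first item under Secondary Endpoints is "Association of (real world or predicted) FVIII/FIX levels with bleeding episodes and daily activities". The bleed measures listed there are "total number of bleeds over time, number of spontaneous bleeds, number of traumatic bleeds, number of joint bleeds, number of target joint bleeds, and bleed" severity. The Statistical Analysis section gives this endpoint one sentence: "Association of factor levels with bleedings will be described according to sub classifications". It then adds a paired comparison of the annualized bleeding rate (ABR) and joint status before and during PK guidance.

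The Interventions section says of the retrospective data, where detailed logs were kept, that annualized bleeding rates can be calculated together with "FVIII/FIX trough levels and FVIII/FIX levels during physical activities and at the onset of a bleed can be calculated". For the prospective part it says: "Only if clinically indicated, FVIII/FIX levels will be measured during bleeds". It justifies the 24-week follow-up by the need to establish how levels and bleeding are associated.

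The aim is stated more strongly elsewhere. The Abstract promises to "provide evidence to more clearly associate factor activity levels with bleeding risk", and the Pharmacokinetic-Guided Dosing section says that "factor levels can be predicted at any time point and related to bleeding and activity". No section names time spent at a level, a bleed rate by level, or level as a time-varying exposure.

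**The concern.** A bleed at a given level can occur only during the hours spent at that level. Within one dosing interval the level falls through several bands and stays in each for a different length of time. The distribution of levels at bleed onset is therefore time at level multiplied by the bleeding rate at that level, and without the time the two factors cannot be separated. Subclassifying by bleed type does not help, because it divides the bleeds and leaves the patient-time undivided. A calendar-time rate such as the ABR averages over the whole curve.

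This is distinct from confounding through the choice of target level: it arises within a single patient whose regimen never changes.

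Two misreadings are possible. A real excess risk at low levels may look unimportant because most bleeds occur at higher levels, where most of the time is spent. Groups with different curves, such as the SHL and EHL strata, may also show different onset levels with no difference in how risk depends on level. The association is the stated reason for 24 of the 36 treatment weeks.

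**Working it through.** The article gives no figure for this association, so there is nothing to reproduce. The check shows the mechanism under assumed pharmacokinetics.

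**Inputs from the article:** 12 + 24 weeks of treatment (Interventions); at least 50 patients (Sample Size Calculation); 0.05 IU/mL as the upper limit of the moderate-to-severe range (Introduction).

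**Assumed, not in the article:** mono-exponential decline to a zero baseline, with the peaks, half-lives, dosing intervals and rate ratios shown below.

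**Step 1. Time below 0.05 IU/mL.** With half-life h and interval τ, the share of time below 0.05 is p = 1 − (h/τ) × log2(peak/0.05). If level has no effect on bleeding, p is also the share of bleeds below 0.05.

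| Peak (IU/mL) | h | τ | Time to reach 0.05 | p |
|---|---|---|---|---|
| 0.60 | 12 h | 48 h | 12 × log2(12) = 43.0 h | 10.4% |
| 0.80 | 18 h | 96 h | 18 × log2(16) = 72.0 h | 25.0% |
| 0.60 | 8 h | 48 h | 8 × log2(12) = 28.7 h | 40.3% |

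The share of bleeds at low levels moves from about 10% to 40% with no level effect at all. A longer assumed interval widens this further: peak 0.60, h = 10 h, τ = 72 h gives 50.2%.

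**Step 2. A real effect that looks small.** If the rate below 0.05 is R times the rate above it, the share of bleeds below 0.05 is R·p / (R·p + 1 − p). With p = 0.104 and R = 3: 0.312 / (0.312 + 0.896) = 25.8%. So 74% of bleeds still occur above 0.05 although the rate ratio is 3.

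**Step 3. Same picture, different truth.** Take the share of bleeds at 0.01–0.05 IU/mL, peak 0.60.
- h = 12 h, τ = 72 h, no level effect: 38.7%.
- h = 10 h, τ = 48 h, rate doubled in that band: time share 25.3%, so 2 × 0.253 / (2 × 0.253 + 0.747) = 40.4%.

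Raw onset levels give nearly the same figure for no effect and for a doubled rate.

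**Step 4. The denominator resolves it.** With h = 12 h, τ = 72 h and assumed relative rates 3 : 2 : 1 for <0.01, 0.01–0.05 and ≥0.05, bleed share divided by time share is 2.12, 1.41 and 0.71, which is 3 : 2 : 1. With no effect, the ratio is 1.00 in every band.

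**Step 5. Information available.** 50 × 36/52 = 34.6 patient-years. At an assumed 1 to 4 bleeds per patient-year this gives about 35 to 138 bleeds, so estimates by band will be imprecise.

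**The case against.** The strongest reply is that the article does not fix a wrong analysis; it fixes very little. A reader might infer that the association will rest only on bleed counts and onset levels. The documents do not support that. The endpoint covers observed or predicted levels, the article notes that levels can be predicted at any time, and onset level as a calculated outcome is named for the retrospective data, beside trough levels and annualized rates. A reader might also infer that onset levels show only where patients spend their time. That too goes too far, since they carry the bleeding rate as well: in Step 2 the share below 0.05 rises from 10.4% to 25.8%.

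Nor is the plan without any denominator. Bleeds over time and the ABR are rates, and comparing them with trough level between patients is not distorted in the way shown here. Level bands and regression models are often left to a full protocol or analysis plan, which is not shown. The figures rest on assumed FVIII curves, cover no FIX product, and ignore the endogenous level of non-severe patients, which would change the time below 0.05. Person-time alone would not remove confounding by activity, because physicians may set peak targets for intensive activity.

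All of this stands, and it limits the point. It does not remove it: the analysis that is stated is a description by bleed type, and that analysis falls short of the stated claim about risk.

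**Conclusion.** The point holds in a limited form. The stated analysis allows a description of bleeds by type and a between-patient comparison of bleed rate with trough level. It does not allow bleeding risk at a level to be told apart from time spent at that level, so it does not support the Abstract's wording on bleeding risk. The Conclusion's more modest aim of better insight into the association is easier to meet.

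The size cannot be fixed from the article: the 10% to 40% range rests on assumed peaks, half-lives and intervals, mono-exponential decline and no endogenous level. The endpoint is secondary and the remedy is cheap, so this is a recommended improvement. The primary endpoint is unaffected.

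**What to change.** In the Statistical Analysis section, replace the descriptive sentence with a statement along these lines:

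- Predicted levels over all follow-up will be computed for each patient from the logged infusions and the individual PK parameters.
- Total, spontaneous and joint bleeds will be reported per person-time in a few prespecified level bands, for example <0.01, 0.01–0.05, 0.05–0.20 and ≥0.20 IU/mL.
- Rate ratios will come from a Poisson or negative binomial model with log person-time in the band as offset, or from a recurrent-event model with predicted level as a time-varying covariate, in either case with clustering by patient.
- Results will be labelled exploratory, because bands will be sparse with about 50 patients and activity can confound the association.
- Levels at bleed onset will be kept as a descriptive listing.

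If this is not done, limit the claim in the Abstract to a description of levels and bleeds.

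The cost is wording and programming. Patients who cannot keep infusion and bleed logs are already excluded, and individual PK parameters are already estimated, so no new data, visits or patients are needed. The drawback is wide intervals.
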